#### Primary outcome: average pain intensity

The primary outcome will be change from pre-treatment to post-treatment in average pain intensity over the past week assessed using an 11-point NRS, where 0 means “No pain” and 10 means “Pain as bad as you can imagine.” The NRS has consistently demonstrated its validity as a measure of pain intensity through its strong association with other measures of pain intensity as well as its sensitivity to detect changes in pain associated with pain treatment [27]. It has been validated in the MS population [21] and is considered a primary outcome measure for pain clinical trials per the recommendations of an expert consensus panel [27].

#### Secondary outcomes

Secondary outcome domains will include pain interference and the key co-morbid symptoms of fatigue, sleep, and depressive symptoms (see Table 1). Physical function, self-efficacy for managing pain, and quality of life will also be assessed at each time point.

#### Moderator domains

The primary moderator variables will be catastrophizing, mindfulness, and behavioral activation (Table 1). Exploratory moderators include demographic variables (sex, age), pain characteristics (pre-treatment pain intensity, pain type (neuropathic versus non-neuropathic pain)), baseline cognitive functioning, treatment expectancies, and baseline levels of the study outcomes and co-morbid symptoms (depressive symptoms, fatigue, and sleep disturbance).

#### Descriptive and process measures

As shown in Table 1, a range of demographic and clinical variables will be assessed pre-treatment to characterize the sample. These will include postal zip code as an indicator of rurality. Participants will complete measures of pain variables and MS disease characteristics in order to characterize their clinical status pre-treatment. Measures of MS disease were drawn from the National Institute of Neurologic Disorders and Stroke Common Data Elements for MS. [19] MS diagnosis, date of diagnosis, and course will be confirmed with participants’ providers. We will also obtain information about pain treatments (pharmacologic and nonpharmacologic) at each outcome assessment to allow us to describe treatment use in all three groups, including usual care.

The study therapists will complete an adherence log after each group session, which will include the number and duration (in minutes) of sessions attended by those assigned to MBCT or CBT. Participants allocated to one of the two active treatment groups will complete measures of therapeutic alliance (with the group therapist) and group climate (group engagement), as these may influence outcomes and thus be described and included in analyses.

### Statistical power

The primary study outcome variable will be change in average pain intensity, as represented by the difference between the pre-treatment and post-treatment average pain intensity measures. Anticipated effects for CBT and usual care are based on the changes observed in our previous CBT trials using the 0–10 NRS. Anticipated effect sizes for MBCT are based on published studies of the effects of treatments involving mindfulness in which 0–10 NRS measures were used. Assuming a decrease in pain score of 0.3 points in the usual care group, 0.8, 1.0, and 1.4 in the CBT group, and 0.6, 0.8, and 1.0 in the MBCT group, we calculated the sample size to find differences between pre-treatment and post-treatment differences in scores, with alpha of 0.05, power of 0.80, and varying the standard deviation (SD) from 0.15 to 1 (to cover values observed). Sample sizes of 68 completers per condition will provide at least 80% power, even at the largest standard deviation, to detect a significant between-group effect for pre-treatment to post-treatment changes in average pain intensity.

### Statistical analyses

We will report the number of participants approached (and recruitment source), eligible, excluded, declined, enrolled, randomized, and who provided data at each assessment point (including reasons for exclusion, declination, etc.). We will examine distributions of all variables for outlying values and skewness; where indicated, variables will be recoded or transformed. We will use descriptive statistics to summarize all data, including demographic, clinical, primary, secondary, and moderator variables. We will summarize intervention information, including session adherence, duration, and homework completion, as well as fidelity indicators.

Next, we will identify patterns in missing data. If there are very few missing data, we will analyze the complete dataset. If there is a substantial number of missing values in the outcomes (say, about 5% or more), we will need to decide if the data are missing completely at random (MCAR), i.e., missing data are independent of observable variable and unobservable parameters, and occur at random, or missing at random (MAR), i.e., missing values do not occur at random, but can be modeled by variables that have complete information, in which cases the analysis of the complete dataset still provides unbiased estimators. Both MCAR and MAR cannot be verified statistically, and assumptions need to be made. For example, if missing data for pain post-treatment were missing because those individuals had higher levels of pain, the missing pattern would not follow MCAR or MAR, and therefore would be non-ignorable. If this situation happens, we will implement multiple imputation procedures, where several imputed datasets will be created and analyzed, and their results combined. We propose 50 multiple imputations (the literature suggests 20–100) [41]. However, we will implement various checks in the protocol in order to minimize the number of missing values. We do not plan to conduct interim analyses and therefore do not have any stopping guidelines.

#### Testing hypothesis 1

We will use an intent-to-treat approach to test hypothesis 1: all randomized participants will be included based upon their assigned treatment group regardless of actual treatment received and adherence. Hypothesis 1 states that participants randomly assigned to MBCT or CBT will report significantly greater reductions in average pain intensity relative to participants assigned to usual care, post-treatment (primary endpoint). This will be tested using analysis of covariance, with treatment condition (MBCT, CBT, usual care) as the explanatory variable, the pre-treatment average pain intensity score as the covariate, and change from pre-treatment to post-treatment score in average pain intensity as the response variable. Support for hypothesis 1 would emerge if after controlling for the pre-treatment pain score, there are differences in the response variable by intervention group, and subsequent post-hoc analyses comparing the adjusted means indicate greater reductions in pain intensity in the MBCT and CBT conditions, relative to the usual care condition. Although we anticipate that MBCT and CBT will have similar effects on the primary outcome variable, these analyses will also allow us to compare, as an exploratory test, the relative effects of MBCT and CBT. Effect sizes will be computed and reported. Secondary outcomes will be assessed using similar analyses to those used to test hypothesis 1.

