## Methods/design

### Overview

This study is a three-group parallel (1:1:1), single-blind, randomized controlled trial comparing two-group-based, videoconference-delivered, nonpharmacologic pain treatments to usual care (see Fig. 1). Specifically, we will compare eight sessions of videoconference group delivery of MBCT and CBT to usual care for chronic pain in 240 adults with MS. Self-report measures of average pain intensity (primary outcome) and secondary outcomes will be assessed pre-treatment, mid-treatment, post-treatment, and at 6-month follow up. The MBCT and CBT intervention groups will start at the same time during week 1. Patients will be randomized immediately after the pre-treatment assessment.

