### Study interventions and usual care condition

Both active interventions will consist of eight 2-h, group-based sessions delivered by postdoctoral psychology fellows, licensed psychologists, or a masters-level social worker (the “therapist”). Group delivery requires less therapist time (i.e., one therapist can treat 6–9 patients at once) and therefore may be more easily implemented in community settings in greater numbers of people with pain and MS. Group delivery also has the advantage of allowing participants to learn and obtain support from one another. The sessions will be offered at a variety of times (morning, afternoon, evening, weekend) to reduce barriers to participation and encourage adherence.

The interventions will be delivered in groups of 6–9 participants using the HIPAA-compliant Internet Zoom platform (https://zoom.us/). Zoom-hosted videoconferences allow all participants to see and hear one another. They also allow screen sharing, giving therapists the opportunity to display visual information (e.g., PowerPoint slides with session content) for all participants to view during the sessions. In the event that a participant cannot access the videoconference during any particular session, we will provide participants with a workbook (electronic and/or paper format) to follow during the sessions and facilitate skills practice outside of treatment sessions. Zoom also allows participants to call into the audioconference portion of the session in the event that they are unable to gain online access for any reason. Although both MBCT and CBT are compatible with either group or individual, face-to-face delivery, we adapted both for videoconference delivery via the Zoom platform (e.g., includes slides of in-session activities shared using screen-sharing).

Participants in any of the three conditions will not be encouraged or prohibited from using other pharmacologic or nonpharmacologic pain treatments. At each outcome assessment we will collect information about participants’ use of other concomitant treatments (pharmacologic and nonpharmacologic) to allow us to describe and compare treatment use across all three groups, including usual care. There will be no special criteria for discontinuing or modifying allocated interventions.

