#### Usual care

Participants randomly assigned to usual care will be contacted by telephone by a staff member not involved in data collection who will inform them of their allocation to usual care. Study personnel will not make any further attempts to influence usual care participants’ pain management or health care unless a psychiatric emergency arises (e.g., suicidal ideation is detected at an outcome assessment). Individuals assigned to usual care will be offered the opportunity to participate in their choice of either MBCT or CBT after they have completed their obligations for study data collection (i.e., after the 6-month follow up assessment). This will ensure that all study participants have the opportunity to receive an active treatment and increase retention of participants in the usual care control group.

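### MBCT and CBT are delivered in therapist-led groups of 6–9, but the primary ANCOVA and the power calculation treat participants as independent; if outcomes correlate within groups, standard errors are too small

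*Protocol article*

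**What the plan says.** **Delivery.** Under Study interventions and usual care condition, both active arms receive eight 2-hour sessions: "The interventions will be delivered in groups of 6–9 participants using the HIPAA-compliant Internet Zoom platform". A single leader serves the whole group ("one therapist can treat 6–9 patients at once"), and interaction is presented as a benefit: "Group delivery also has the advantage of allowing participants to learn and obtain support from one another". Under Descriptive and process measures, therapeutic alliance and group climate are collected in the active arms because they may affect outcomes. Usual care has no sessions: "Participants randomly assigned to usual care will be contacted by telephone by a staff member not involved in data collection".

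**Analysis.** Under Testing hypothesis 1: "This will be tested using analysis of covariance, with treatment condition (MBCT, CBT, usual care) as the explanatory variable". The covariate is baseline average pain and the response is change to post-treatment. Hypothesis 1 is supported if the conditions differ and post-hoc comparisons then favour MBCT and CBT over usual care. The same model gives the exploratory MBCT versus CBT comparison, and secondary outcomes use similar analyses.

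**Power.** Under Statistical power: "Sample sizes of 68 completers per condition will provide at least 80% power". The text says this holds at the largest SD considered, which is 1. It mentions no ICC or design effect.

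**The concern.** This is a partially nested design. Participants are randomised individually, but those in MBCT and CBT then share a therapist and fellow group members for the whole course, while those in usual care do not. Shared exposure can make outcomes within a group alike, and the article itself expects group and therapist influences. An ANCOVA with only arm and baseline pain assumes independent residuals. If they are positively correlated within groups, the variance of each active-arm mean is understated. Confidence intervals for the primary contrasts are then too narrow and p-values too small, and the planned sample carries less information than the power statement assumes.

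**Working it through.** **Inputs from the protocol article:** group size m = 6 to 9; 68 completers per arm (204 of 240, i.e. 85%); alpha 0.05 (sidedness not stated, two-sided assumed); smallest CBT versus usual care difference 0.8 − 0.3 = 0.5; largest SD 1. **Assumed:** ICC 0.01, 0.05 and 0.10.

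**Step 1: the plan's figure under independence.** SE = √(2/68) = 0.1715, and power = Φ(0.5/0.1715 − 1.96) = 83%. The statement of at least 80% therefore reproduces for the 0.5 difference. It does not reproduce for the smallest MBCT difference (0.6 − 0.3 = 0.3), where power is 42%. That is a separate matter from clustering.

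**Step 2: number of groups.** 68/9 to 68/6 gives about 8 to 11 groups per active arm; 80/9 to 80/6 gives about 9 to 13.

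**Step 3: standard errors and error rates.** The design effect in a grouped arm is DE = 1 + (m − 1) × ICC. The ratio of true to stated SE is √((1 + DE)/2) for active versus usual care and √DE for MBCT versus CBT. The actual rate of a nominal 5% test is 2 × (1 − Φ(1.96/ratio)). The null is that the arm's average effect is zero while effects vary between groups.

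| ICC | DE (m = 6 to 9) | SE ratio, active vs usual care | Error rate, active vs usual care | Error rate, MBCT vs CBT |
|---|---|---|---|---|
| 0.01 | 1.05–1.08 | 1.01–1.02 | 5.3–5.5% | 5.6–5.9% |
| 0.05 | 1.25–1.40 | 1.06–1.10 | 6.5–7.4% | 8.0–9.8% |
| 0.10 | 1.50–1.80 | 1.12–1.18 | 8.0–9.8% | 11.0–14.4% |

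**Step 4: power for the 0.5 difference, 68 per arm.** SE = √((1 + DE)/68). For example, at m = 6 and ICC 0.05: √(2.25/68) = 0.1819, and Φ(0.5/0.1819 − 1.96) = 78.5%. The completers needed per arm for 80% are (1 + DE) × ((1.96 + 0.84)/0.5)².

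| ICC | Power | Completers per arm for 80% |
|---|---|---|
| 0 | 83% | 63 |
| 0.01 | 82% | 65–66 |
| 0.05 | 76–79% | 71–76 |
| 0.10 | 69–74% | 79–88 |

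**Step 5: the stated decision rule.** I simulated the stated ANCOVA with 80 per arm, 10 groups of 8 in each active arm, no average effect, and 40,000 runs per ICC.

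| ICC | Omnibus F rejects | Omnibus plus at least one active arm better | Omnibus plus both active arms better |
|---|---|---|---|
| 0 | 5.0% | 2.1% | 0.4% |
| 0.05 | 8.8% | 3.5% | 0.5% |
| 0.10 | 12.9% | 5.3% | 0.7% |

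With 68 per arm and groups of 6 to 9, the simulated omnibus rate is 7.7–9.0% at ICC 0.05 and 11.1–13.8% at ICC 0.10.

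**The case against.** **The ICC may be zero.** The article gives none. At zero nothing is inflated, and at 0.01 the effect is slight. Likewise, if treatment, group and therapist affect nobody, individual randomisation keeps the ANCOVA approximately valid. Both points stand, so the finding is conditional on a positive ICC.

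**The omnibus rate overstates the risk to hypothesis 1.** A reader might take 9% or 13% as the false-positive rate for the primary claim. The documents do not support that, because the rule also requires post-hoc superiority over usual care; under the global null it stays at or below about 5%. The rule does not repair the standard errors, however: the individual contrasts and their intervals remain affected, notably when one active arm works and the other does not.

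**The largest figures belong to an exploratory comparison.** The article labels MBCT versus CBT exploratory, so those rates should not set the weight of the finding.

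**Retention may exceed 85%.** The article cites 90–98% in similar trials, which is about 72 to 78 of 80 per arm. At m = 7.5, power is then 79.5–82.5% at ICC 0.05 and 74–77% at ICC 0.10. The loss shrinks but remains at the top of the assumed range.

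**Moderation.** A reader might extend the inflation to hypotheses 2a–2c. The moderators are individual baseline scores that vary within groups, and simulation with a group random intercept put the unclustered arm-by-moderator test at about 5% (4.9–5.3%). No inflation is shown there.

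**Closed groups.** The article does not call the groups closed; it says only "The MBCT and CBT intervention groups will start at the same time during week 1". The argument needs only shared groups and therapists.

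**Could this be left to the analysis plan or the process measures?** The article fixes the primary model's factor, covariate and response, and it fixes the sample size. A group effect changes the stated model and is more than detail within it. Alliance and group climate arise after randomisation and only in the active arms, so adjusting for them would not model within-group correlation.

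**Conclusion.** The point holds conditionally. The grouped delivery and the lack of any allowance for it are plain in the text, and for any positive ICC the direction of the error is certain. Its size is not known. Over an assumed ICC of 0.01 to 0.10 and groups of 6 to 9, a nominal 5% test of an active arm against usual care runs at 5.3% to 9.8%, and the power margin at 68 per arm is lost from about ICC 0.05. The documents do not support saying that the trial's type I error does exceed 5%, or that hypothesis 1 has a 9–13% false-positive rate. Because the primary intervals and p-values are affected, the model should be settled before the data are analysed.

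**What to change.** For hypothesis 1 and the secondary outcomes:

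- Keep the same fixed effects and add a random intercept for therapy group in MBCT and CBT only, with each usual-care participant as a singleton.
- Use small-sample degrees of freedom (Kenward–Roger or Satterthwaite, for example).
- If therapists lead several groups, consider a therapist term as well.
- Keep the group term whatever its estimate, and report the ICC.
- Restate power under an assumed ICC.

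Using the same model for moderation is optional, for consistency.

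**Cost.** The change needs wording and each participant's group identifier, with no new measurements; therapists already log attendance after each group session. Intervals will be slightly wider, and with about 8 to 13 groups per active arm the ICC will be imprecisely estimated, which is why the small-sample degrees of freedom are needed.

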### Randomization, allocation concealment, and procedures to minimize bias

Enrolled participants who complete the pre-treatment assessment will be randomly assigned to one of the three conditions. The trial manager is not involved in any outcome assessments and therefore will carry out randomization following the protocol designed by the study biostatistician ([name]) prior to the study’s start. Participants will be randomized in stratified blocks using a computer-generated, password-protected randomization list, with randomization stratified by sex and pre-treatment pain intensity (mild/moderate or severe) to control for variation in outcome attributable to each stratification variable. The trial manager will notify participants of their allocation. All staff involved in data collection and management will be kept unaware of the participants’ group assignments and will explicitly inform participants that they (staff) are to remain blinded during the course of the study. The biostatistician will also be unaware of treatment assignment. Participants will be informed that the CBT and MBCT are each a type of pain self-management intervention and that the study’s purpose is to determine which treatment is more beneficial. Thus, only the staff involved in data collection and management are blinded, whereas study participants and the trial manager will have access to group allocation. We do not anticipate any requirement for unblinding during the course of the trial.

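### Randomization is stratified by sex, but the primary ANCOVA adjusts only for pre-treatment pain, so if sex is prognostic the reported standard error is slightly too large

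*Protocol article*

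**What the plan says.** In the protocol article, the section on randomization, allocation concealment and bias describes blocked allocation from a prepared list. It names the factors and their purpose as follows: "with randomization stratified by sex and pre-treatment pain intensity (mild/moderate or severe) to control for variation in outcome attributable to each stratification variable". Two design factors are thus named, and the reason given is the same for both.

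Under Testing hypothesis 1, the primary model is written out. Its form is "analysis of covariance, with treatment condition (MBCT, CBT, usual care) as the explanatory variable". Only one adjustment variable is listed: "the pre-treatment average pain intensity score as the covariate". The outcome being modelled is the change in average pain from before to after treatment. The same paragraph describes support for the hypothesis as a difference between groups after adjustment for the pre-treatment pain score, and says that secondary outcomes will be analysed in a similar way.

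Sex appears elsewhere as a demographic variable in Table 1 and in the list under Moderator domains: "Exploratory moderators include demographic variables (sex, age". The article neither adds sex to the primary model nor gives a reason for leaving it out.

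**The concern.** Stratified blocks hold the sex mix nearly equal across arms. If sex is related to outcome, this makes the difference between arms less variable than under simple randomization. A model without sex cannot recognise that gain. Sex-related variation stays in the residual, and the standard error is computed as if the arms could have differed by chance in their sex mix. The confidence interval is then a little too wide, and the test rejects less often than its nominal level.

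The article treats its two factors differently. Pain is stratified on and adjusted for; sex is stratified on for the same stated reason and then dropped. At stake is a small amount of power in the confirmatory test, and the same in the secondary-outcome models.

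**Working it through.** **Inputs from the article.** 68 completers per arm (204 in all); alpha 0.05, taken as two-sided because the article does not say; largest SD 1 ("with alpha of 0.05, power of 0.80, and varying the standard deviation (SD) from 0.15 to 1"); "Assuming a decrease in pain score of 0.3 points in the usual care group, 0.8, 1.0, and 1.4 in the CBT group"; and decreases of 0.6, 0.8 and 1.0 for MBCT. The smallest CBT difference from usual care is 0.8 − 0.3 = 0.5 points.

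**Assumed input.** R² is the share of residual variance, after baseline pain, that sex explains. The article gives no value, so I use 0 to 0.10.

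**Step 1: the plan's own figure.** For a difference of 0.5 and SD 1, n per arm = 2(1.96 + 0.842)²/0.5² = 62.8, so 63 (64 by t-test). With 68 per arm the standard error is √(2/68) = 0.1715 and power is Φ(0.5/0.1715 − 1.96) = 83.0%. The claim of at least 80% holds for this difference, though no variant tried returns exactly 68. It fails for the smallest MBCT difference, 0.6 − 0.3 = 0.3, where power is 41.7%. That is a separate matter, and adding sex does not repair it (45.4% at R² = 0.10). The step from 204 to 240 reproduces: 204/0.85 = 240.

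**Step 2: effect of leaving sex out.** With sex balanced by design:

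- Reported SE / true SE = 1/√(1 − R²)
- Actual type I error without sex = 2[1 − Φ(1.96/√(1 − R²))]
- Power with sex = Φ(0.5/(0.1715√(1 − R²)) − 1.96)

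| R² (assumed) | SE overstated by | Actual type I error without sex | Power with sex | n per arm for 80% power, with sex |
|---|---|---|---|---|
| 0 | 0% | 5.0% | 83.0% | 63 |
| 0.01 | 0.5% | 4.9% | 83.4% | 63 |
| 0.02 | 1.0% | 4.8% | 83.8% | 62 |
| 0.05 | 2.6% | 4.4% | 84.9% | 60 |
| 0.10 | 5.4% | 3.9% | 86.7% | 57 |

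Against the nominal 83.0%, the gain is 0 to 3.7 points. Part of that comes from the stratification itself. At R² = 0.10 the true SE is 0.1715 × √0.90 = 0.1627, so the model without sex has power Φ((0.5 − 1.96 × 0.1715)/0.1627) = 84.3%. The net gain from adding sex is then 86.7 − 84.3 = 2.4 points.

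**Step 3: simulation.** 204 patients, blocks stratified by sex and pain severity, 75% in one sex category (assumed), 4,000 runs per setting.

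| R² | Model | Mean reported SE | Power (difference 0.5) | Type I error |
|---|---|---|---|---|
| 0.05 | without sex | 0.171 | 82.4% | 4.5% |
| 0.05 | with sex | 0.167 | 84.0% | 5.2% |
| 0.10 | without sex | 0.171 | 83.7% | 4.0% |
| 0.10 | with sex | 0.163 | 86.5% | 4.7% |

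The empirical SD of the treatment estimate was the same with and without sex: 0.169 in both models at R² = 0.05 and 0.164 in both at R² = 0.10 (no-effect runs). The estimate does not change in precision; only its reported standard error does.

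**Step 4: what these R² values mean.** With SD 1 and a fraction p in one sex, the sex difference in mean change is √(R²/(p(1 − p))). For p from 0.50 to 0.75, R² = 0.02 needs 0.28 to 0.33 points, 0.05 needs 0.45 to 0.52, and 0.10 needs 0.63 to 0.73. A sex difference of 0.25 points at p = 0.75 gives R² = 0.25² × 0.1875 = 0.012, an SE overstated by about 0.6% and a type I error of about 4.9%.

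**The case against.** The strongest reply is that the loss is conditional and probably small. It is zero if sex does not predict change in pain beyond baseline pain, and the article gives no figure. By step 4, the upper end of the range needs a sex difference as large as, or larger than, the 0.5-point treatment effect in the power section. The error is also in the safe direction. All of this stands and limits the size of the point.

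A second reply is that covariates are often settled in the analysis plan, which is not shown. This carries little weight here, because the article writes out the primary model and names one covariate in the singular.

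A reader might infer more than the article supports:

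- **That the purpose of stratifying is defeated, or the estimate is less precise.** The article attaches that purpose to the randomization, and stratified blocks keep sex-related variation out of the arm contrast whatever the model. The simulation shows an equally variable estimate either way. Only the reported SE fails to credit the balance.
- **That the result is biased or the test too liberal.** Neither follows; the test is conservative.
- **That the moderation and imputation models are wrong for lacking sex.** The article fixes no full covariate set for the former and names no variables for the latter. The balance argument also does not carry over to treatment-by-moderator interactions, since stratifying by sex does not balance the moderators.

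**Conclusion.** The point holds as a minor mismatch between the randomization and the primary analysis. Sex is a stratification factor, the primary ANCOVA leaves it out, and no reason is given. If sex is prognostic beyond baseline pain, the reported SE is too large by up to 5.4% and the actual type I error falls as low as 3.9% over the assumed range. The gain in power is at most about 4 points against the nominal 83.0%, or about 2.4 points against what the model without sex achieves under stratified allocation. If sex is not prognostic, nothing is lost.

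These figures rest on a two-sided test, SD 1, 68 completers per arm, an assumed R² for sex, and sex staying balanced among those analysed. No conclusion of the trial is threatened. The change is worth making because it costs almost nothing and follows from the article's own reason for stratifying.

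**What to change.** State that the hypothesis 1 ANCOVA includes sex as a fixed effect together with continuous pre-treatment average pain, and that the secondary-outcome models patterned on it do the same. The continuous pain score already covers the pain stratum, so the severity category need not be added. If sex is to stay out, give the reason.

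The cost is one sentence and about 1 degree of freedom out of about 200. Sex is known for every participant before randomization, so no further data are needed. The change should be fixed before outcome data are analysed.
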